### 3) Number of Subjects and Rationale

This study is a prospective pilot investigator-initiated clinical trial. The results obtained from this study will be used to calculate the number of participants for future confirmatory clinical trials. A total of 100 subjects will be recruited, with 50 in the treatment group (receiving Kyung-Ok-Go) and 50 in the control group (receiving placebo).

| Institute                                       | Treatment group | Control group | Sum |
|-------------------------------------------------|-----------------|---------------|-----|
| Kyunghee University
Korean Medicine Hospital | 30              | 30            | 60  |
| Dongueui University
Korean Medicine Hospital | 20              | 20            | 40  |
| Sum                                             | 50              | 50            | 100 |

### 8 . Standard Treatment Method for Target Disease

Various methods, including medications, alternative medicine, cognitive-behavioral therapy, and exercise, are currently being attempted to alleviate the fatigue symptoms following COVID-19 infection. Some studies have suggested that rintatolimod, a drug used to treat chronic fatigue syndrome, as well as counseling and graded exercise therapy, may offer

benefits, but the evidence for these interventions remains limited. The CDC describes the fatigue following COVID-19 under the category of Chronic Fatigue Syndrome/Myalgic Encephalomyelitis (CFS/ME), focusing on symptom management through gentle exercises such as meditation and yoga, counseling, dietary supplements, and rest [18]. The UK's NHS also recommends rest, reduced activity levels, graded rest and exercise, sleep management, a balanced diet, and concentration training as part of symptom management [19].

**9 . Investigational Medicinal Product****9.1 Investigational drugs Code name, Quantity of raw material of medicine , dosage form**

(appearance), etc.

**Test drug**

|                                        |                                                                   |                              |        |      |
|----------------------------------------|-------------------------------------------------------------------|------------------------------|--------|------|
| Code name
(product name)    | CV1 ( Jin Kyungok-go)                                             |                              |        |      |
| Manufacture
company         | Kyungjin Pharmaceutical Co., Ltd.                                 |                              |        |      |
| Route of
administration     | Oral-                                                             |                              |        |      |
| Form and
appearance         | Black-brown viscous soft extract filled in aluminum stick pouches |                              |        |      |
| Ingredients and
Composition | Per 112.5g of this medicine                                       |                              |        |      |
|                                        | Raw material
name                                              | standard                     | amount | unit |
|                                        | Fresh
Rehmannia
glutinoso juice                             | Attachment
specifications | 39.9   | g    |
|                                        | Poria                                                             | K.P.                         | 12.4   | g    |
|                                        | Ginseng                                                           | K.P.                         | 6.2    | g    |
|                                        | Honey                                                             | J P                          | 41.5   | g    |
| Expiration date                 | 36 months from date of manufacture                                |                              |        |      |
| Storage method                  | Airtight container, store at room temperature (1~30°C)            |                              |        |      |

**placebo**

|                                     |                                   |
|-------------------------------------|-----------------------------------|
| Code name
(product name) | P ( placebo)                      |
| Manufacture
company      | Kyungjin Pharmaceutical Co., Ltd. |
| Route of                     | Oral-                             |

|                                    |                                                                   |                         |        |      |
|------------------------------------|-------------------------------------------------------------------|-------------------------|--------|------|
| administration              |                                                                   |                         |        |      |
| Form and appearance         | Black-brown viscous soft extract filled in aluminum stick pouches |                         |        |      |
| Ingredients and Composition | Per 112.5g of this medicine                                       |                         |        |      |
|                                    | Raw material name                                                 | standard                | amount | unit |
|                                    | Purified water                                                    | K.P.                    | 65.0   | g    |
|                                    | Sodium benzoate                                                   | K.P.                    | 0.06   | g    |
|                                    | Citric acid hydrate                                               | K.P.                    | 0.09   | g    |
|                                    | Sodium citrate hydrate                                            | K.P.                    | 0.04   | g    |
|                                    | High fructose 55                                                  | Attached specifications | 21.0   | g    |
|                                    | White sugar                                                       | K.P.                    | 14.0   | g    |
|                                    | Caramel                                                           | NF                      | 5.0    | g    |
|                                    | Xanthan gum                                                       | EP                      | 3.8    | g    |
|                                    | Concentrated glycerin                                             | K.P.                    | 3.5    | g    |
|                                    | Ginseng Fureba A - 980306                                         | Attached specifications | 0.01   | g    |
| Expiration date             | 36 months from date of manufacture                                |                         |        |      |
| Storage method              | Airtight container, store at room temperature (1~30°C)            |                         |        |      |

## 9.2 Rationale for Dosage Selection

The herbal medicine provided in this clinical trial is an authorized medicinal product approved by the Ministry of Food and Drug Safety. The dosage and administration method will strictly adhere to the approved specifications. As indicated in the product approval, CV1 (Jin Kyungok-go) will be administered at a dose of 22.5g (one stick) for adults, twice daily (morning and evening) on an empty stomach or between meals. The placebo will be administered in the

same manner as the test drug, at a dose of 22.5g (one stick) for adults, twice daily (morning and evening) on an empty stomach or between meals.

### 9.3 Packaging and label

Drugs for clinical trials are manufactured by the clinical trial sponsor, packaged and labeled, and supplied to the managing pharmacist of the clinical trial institution. All production and packaging of test and reference drugs are carried out in GMP facilities according to GMP regulations. The label for clinical investigational drugs is written in accordance with Table 11 of the Regulations on Pharmaceutical Manufacturing and Quality Control (enacted on January 1, 2017). A label containing the following information is produced on the packaging of this drug. However, only the (\*) items are indicated on the primary packaging of clinical trial drugs, and all items are indicated on the secondary packaging. In the case of the target allocation number, it is not indicated on the primary packaging . Document the relevant information and keep it.

|                                                                                                                        |
|------------------------------------------------------------------------------------------------------------------------|
| ■ Subject allocation number                                                                                            |
| ■ Reference code *                                                                                                     |
| ■ Name of investigational drug*                                                                                        |
| ■ Expiration date or re-inspection date                                                                                |
| ■ Batch number or code number *                                                                                        |
| ■ Storage conditions                                                                                                   |
| ■ How to take (take)                                                                                                   |
| ■ Name, address, and phone number of the person who has received approval for the clinical trial plan *  |
| ■ Keep out of reach of children.                                                                                       |
| ■ Cannot be used for purposes other than clinical trials (primary packaging is " for clinical trials ")* |

### 9.4 Management of investigational drugs

Responsibility for the receipt, storage, dispensing, and return of clinical trial drugs lies with the principal investigator and the managing pharmacist of the relevant implementing institution. Clinical investigational drugs are delivered to the managing pharmacist (or principal investigator) of the implementation institution, and the managing pharmacist (or principal investigator) must confirm and sign in writing the receipt and quantity of all supplied clinical investigational drugs and manage them appropriately. Clinical trial drugs must be secured and stored in a storage location with limited access, ensure that the clinical trial drugs are administered to research subjects in accordance with the clinical trial protocol, and ensure that the quantity and management of the clinical trial drugs provided to each research subject is regulated. Manage records. The monitor must regularly check the inventory maintained by the researcher or the managing pharmacist to confirm receipt and payment of used clinical trial drugs. The managing pharmacist (or principal investigator) must return the empty packaging paper and remaining amount of the clinical trial medicine provided to the research subject after use, and the clinical trial medicine, unused clinical trial medicine, used/unused packaging paper and medicine returned by the research subject. Return it to the principal investigator.

## **9.5 Concurrent treatment**

### **Acceptable concomitant medications and treatments**

Drug treatment for fatigue (herbal medicine, Prohibit the use of herbal medicines (dry food, etc.) and herbal medicines containing the medicinal ingredients of the test drug. also Limit participation in medical treatment such as cognitive behavioral therapy or counseling. However, exercise to improve general health is permitted.

## 10 . Research period

3 years after IRB approval

## 11 . Research method

### 11.1 Research design

Patients will undergo a screening process to determine their eligibility after receiving a detailed explanation of the clinical trial and signing the consent form. Eligible patients will be randomly assigned to the treatment group (CV1, Jin Kyungok-go) or the control group (placebo) and will receive the respective intervention for 12 weeks. Each participant will visit the study site monthly during the intervention period and will undergo symptom evaluation and specimen collection (e.g., blood samples) after the 12-week intervention period, at which point the study will conclude. Recruitment will be conducted through internal and external advertisements.

### 11.2 Dosage and administration of the herbal medicine

The dosage and administration method for the herbal medicine during the study period are as follows:

[Usage/Dosage]

| Code name (herbal medicine name) | usage | One-time administration unit (dose) |
|----------------------------------|-------|-------------------------------------|
| CV 1 ( Jin Kyungok-go)           | ●/○/● | 1 packet ( 22.5g)                   |
| P ( placebo)                     | ●/○/● | 1 packet ( 22.5g)                   |

●Take, ○Do not take

[ Administration method ]

Administer 2 times a day on an empty stomach or between meals as per the specified method.

### **11.3 Blinding, etc.**

At Visit 0, each subject will be assigned a unique screening number by the researcher. This number will begin with CVS1-01 at Kyung Hee University Korean Medicine Hospital and CVS2-01 at Dong-Eui University Korean Medicine Hospital, and will be assigned in ascending order from the smallest available number. Once assigned, the screening number will not be reused. If a subject is not treated at Visit 1 for any reason, the screening number assignment and the reason for non-treatment will be documented in the Screening Log and the case report form (CRF).

Block randomization will be employed, and the block size will not be disclosed to maintain blinding. An independent statistician will generate random numbers using STATA Version 4.2 (StataCorp LLC., Texas), and these numbers will be sent to the labeling site for the IMPs, where they will be labeled and packaged in the order of randomization. This ensures both the researcher and the subjects are blinded. The probability of allocation to the treatment or control group is 1:1.

To ensure allocation concealment, the IMPs packaged according to the random numbers generated by the independent statistician will be delivered to the trial sites. Subjects who meet the inclusion criteria, do not meet the exclusion criteria, and voluntarily consent in writing will be assigned the lowest available random number in the order of their participation. This number will be recorded in the CRF, and the IMP will be dispensed accordingly.

### **11.4 Observation and inspection items**

#### **1 1.4.1 Clinical trial progress schedule**

##### **11.4.1.1 Visit 0 ( screening visit)**

Participants who apply to join this clinical trial will receive an explanation of the study and then undergo the following tests. Screening tests can be repeated once within the screening period and must be completed before assigning a participant number. If a retest is conducted, the suitability for participation is determined based on the retest results, and the investigator should document the reasons for the retest, the basis for the decision, and the final results in as much detail as possible.

- ① Before enrolling a clinical trial participant, the principal investigator or the person in charge explains the study process and obtains written consent from the participant.
- ② Screening numbers and random assignment numbers are assigned in the order of written consent completion.
- ③ Investigate and record whether the participant is involved in other clinical trials (within the last 30 days), demographic information, medical history (including diabetes), COVID-19 information (date of onset, recovery date, vaccine details including date, manufacturer, doses, and side effects), past fatigue-related history, and current fatigue symptoms. Even if the participant is receiving diabetes treatment, they can join the study if their test results are within controlled ranges (HbA1c within normal range).
- ④ The physical exam covers general condition, nutritional status, skin/mucosa, eyes (excluding vision impairment), ENT, thyroid, lungs, cardiovascular system, abdomen, renal/urinary system, neurological/psychiatric system, spine/extremities/tumors, peripheral circulation, and lymphatic system.
- ⑤ If possible, confirm and document COVID-19 infection status through the following:
  - SMS notifications from the Disease Control and Prevention Agency regarding confirmed cases.
  - Medical records and diagnostic certificates from the time of COVID-19 diagnosis and treatment.
  - PCR test records from the time of diagnosis.
  - Certificates related to COVID-19 diagnosis or release from quarantine issued by public institutions.
- ⑥ Verify current medications.
- ⑦ Measure vital signs.

- ⑧ Conduct an electrocardiogram (ECG) test.
- ⑨ Collect blood samples for laboratory tests and immune and metabolite analysis (laboratory test results within 28 days of the screening visit can be used):
  - Blood chemistry: AST, ALT,  $\gamma$ -GTP, ALP, HbA1c (considered diabetes if abnormal), BUN, creatinine, total bilirubin, glucose.
  - Immunology: COVID-19 specific antibody/neutralizing antibody tests, single-cell transcriptome analysis (scRNA seq.) for immune-related gene expression comparison, FACS for immunophenotyping, serum cytokine levels.
  - Metabolomics: primary and secondary metabolite profiling.
- ⑩ Perform a pregnancy test (urine or serum  $\beta$ -hCG) for women of childbearing potential (test results within 28 days of screening can be used).
- ⑪ Participants follow the investigator's instructions for the following evaluations:
  - Fatigue assessment using FSS.
  - Evaluation of whether fatigue symptoms have persisted for more than four weeks.
- ⑫ Confirm inclusion/exclusion criteria.

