## Schedule Summary

| Visit                                                                      | 0       | One  | 2      | 3      | 4       | UV * |
|----------------------------------------------------------------------------|---------|------|--------|--------|---------|------|
| Week (day)                                                                 | -1 (-7) | 1(0) | 4 (28) | 8 (56) | 12 (84) | -    |
| Visit window (day)                                                         | -       | +2   | ±2     | ±2     | ±2      | -    |
| Written Consent                                                            | ●       |      |        |        |         |      |
| Demographic Survey                                                         | ●       |      |        |        |         |      |
| Participation in Other Clinical Trials                                     | ●       |      |        |        |         |      |
| Physical Exam                                                              | ●       |      |        |        |         |      |
| Medical History                                                            | ●       | ●    |        |        |         |      |
| COVID-19 Diagnosis                                                         | ●       |      |        |        |         |      |
| Concomitant Medication/Treatment                                           | ●       |      |        |        |         |      |
| Vital Signs                                                                | ●       | ●    | ●      | ●      | ●       | ●    |
| Electrocardiogram                                                          | ●       |      |        |        | ●       | ●    |
| Laboratory Test                                                            | ●       |      |        |        | ●       | ●    |
| Immune, Metabolite Test (Blood Collection)                                 | ●       |      |        |        | ●       | ●    |
| Pregnancy Status Evaluation **                                             | ●       |      |        |        |         |      |
| Fatigue Symptom Evaluation ***                                             | ●       |      |        |        |         |      |
| FSS (Fatigue Severity Scale)                                               | ●       |      | ●      | ●      | ●       | ●    |

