### **2) Exclusion criteria**

- Individuals with a history or current condition of diseases that can cause fatigue (e.g., cancer, sleep disorders, chronic hepatitis, liver cirrhosis, chronic renal failure, tuberculosis, asthma, multiple sclerosis).
- Individuals with conditions that can affect drug absorption or metabolism (e.g., dysphagia, clinically significant gastrointestinal disorders, galactose intolerance, Lapp lactase deficiency, glucose-galactose malabsorption).
- Uncontrolled diabetic patients.
- Individuals with a history of allergies to the investigational medicinal product (herbal medicine).
- Individuals with a history of liver or kidney diseases, or blood tests showing AST, ALT, BUN,

or creatinine levels exceeding three times the upper limit of normal.

- Pregnant or breastfeeding women, or those with the potential to become pregnant.
- Individuals who have participated in another clinical trial within 30 days prior to the study.
- Individuals who have taken herbal or herbal medicine (containing the same ingredients as the investigational medicinal product) within two weeks prior to the study.
- Individuals whom the researcher deems unable to participate in the study due to clinically significant psychiatric symptoms, medical conditions, or laboratory findings.

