#### 11.4.1.2 Visit 1 ( start of intervention , Week 1)

If all tests and eligibility assessments are completed during the screening visit, Visit 1 can be conducted on the same day to assign participant numbers. If the screening visit and assignment of participant numbers occur on the same day, overlapping evaluations are performed only once.

- ① Measure vital signs.
- ② Investigate past and current medical history (changes between Visit 0 and Visit 1).
- ③ Assign random numbers.
- ④ Prescribe a four-week supply of the assigned herbal medicine based on the random number.
- ⑤ Participants follow the investigator's instructions for the following evaluations:
  - Assess fatigue severity using a 0-100 VAS.
  - Evaluate fatigue using the Chalder Fatigue Scale (ChFS).
  - Assess quality of life using EQ-5D-5L.
  - Evaluate sleep status using PSQI-K (Korean version of the Pittsburgh Sleep Quality Index).
  - Conduct cognitive function tests using K-MOCA (Korean-Montreal Cognitive Assessment).
  - Evaluate depression using Beck's Depression Inventory (BDI).

- Perform digit span tests (forward and backward).
- Conduct computerized neurocognitive function tests.
- Perform the Short Physical Performance Battery (SPPB).

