##### **14.4.2 Laboratory tests, vital signs**

Vital signs and quantitative laboratory test results, including heart rate variability, will be presented as descriptive statistics before and after administration for each herbal preparation group. Changes will be compared between groups using the independent two-sample t-test or Wilcoxon rank-sum test. Within-group changes will be tested using the paired t-test or Wilcoxon signed-rank test. Additionally, laboratory test results before and after administration will be categorized as normal (including clinically insignificant abnormal) or clinically significant abnormal changes. Changes within groups will be tested using McNemar's test (or McNemar's exact test).

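### Chemistry results up to 28 days older than screening can become the only pre-dose laboratory value; a panel drawn at Visit 0 would give a closer safety baseline at little cost

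*Protocol*

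**What the plan says.** Section 11.4.1.1 item 9 orders blood at Visit 0 for laboratory tests and for the immune and metabolite analyses. In parentheses it adds that "laboratory test results within 28 days of the screening visit can be used". The chemistry list under that item covers AST and ALT and goes on to "HbA1c (considered diabetes if abnormal), BUN, creatinine, total bilirubin, glucose".

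The Schedule Summary marks the row "Laboratory Test" at Visit 0, Visit 4 and unscheduled visits, with nothing at Visit 1. It marks the row "Immune, Metabolite Test (Blood Collection" at Visit 0 as well. Visit 0 is at day -7 and Visit 1 at day 0, with a window of +2 days for Visit 1.

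The chemistry values serve two purposes:

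- **Eligibility.** Section 7 excludes a participant with AST, ALT, BUN, "or creatinine levels exceeding three times the upper limit of normal". HbA1c decides whether diabetes counts as controlled.
- **Safety.** Section 14.4.2 compares quantitative laboratory changes between groups, and tests them within each group by paired t-test or signed-rank test. It also states that "laboratory test results before and after administration will be categorized as normal" or as clinically significantly abnormal, with McNemar's test within each group. The Visit 4 panel in Section 11.4.1.4 is AST, ALT, BUN and creatinine.

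**The concern.** A look-back for outside results is a common convenience for deciding eligibility. Here the same sentence also fixes the safety baseline, because nothing else is measured before dosing. Where the allowance is used, the pre-treatment liver and kidney values may come from several weeks before the first dose. No section requires them to come from the laboratory that runs the Visit 4 samples.

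Section 27 lists liver dysfunction among the rare potential risks, and AST and ALT are scheduled only once before and once after treatment. The within-arm tests have no concurrent control. A rise or fall between the earlier test and the first dose, or a shift between two laboratories' assays, would appear in them as a change under treatment. In the between-arm comparison the same movement adds variance.

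**Working it through.** The protocol states no figure for the age of a laboratory result at first dose, so there is none to reproduce. The check is calendar addition.

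**Inputs**
- Look-back: 28 days, counted from the screening visit (Section 11.4.1.1 item 9).
- Visit 0 to Visit 1: 7 days nominally (Schedule Summary), or 0 days where both are held together (Section 11.4.1.2).
- Visit 1 window: +2 days (Schedule Summary).
- Visit 4: day 84, window ±2 days, so day 86 at the latest.

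**Age of the chemistry value at first dose** = look-back + gap from Visit 0 to Visit 1 + Visit 1 window used.

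| Route | Earlier result accepted | Panel drawn at Visit 0 |
|---|---|---|
| Visits 0 and 1 on the same day | 28 + 0 = 28 days | 0 days |
| Visit 1 on day 0 | 28 + 7 = 35 days | 7 days |
| Visit 1 at the end of its window | 28 + 7 + 2 = 37 days | 7 + 2 = 9 days |

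**Longest interval from the pre-treatment value to Visit 4**, both with the Visit 4 window used in full:
- Earlier result: 28 + 7 + 84 + 2 = 121 days.
- Panel at Visit 0: 7 + 84 + 2 = 93 days.
- Difference: 121 - 93 = 28 days.

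Without the window the pair is 119 and 91 days, and the difference is again 28. If Visit 4 were counted from a Visit 1 held two days late, both figures would rise by 2 and the difference would not move.

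**Is there another pre-dose value?** Section 11.4.1.2 lists no laboratory test at Visit 1. Section 11.4.1.1 lets screening tests be repeated once but does not require it. When an earlier result is accepted, it is therefore the only scheduled pre-dose value.

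**Is a needle used at Visit 0 anyway?** The schedule and item 9 both place the immune and metabolite draw there. Section 22 agrees: it pays 100,000 KRW at two visits with a blood draw, names Visit 4 as one, and pays 50,000 KRW at Visits 1, 2 and 3. By elimination the other is Visit 0.

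**Effect on the tests.** For a measurement with standard deviation σ at both times and correlation ρ between them, the change has standard deviation σ√(2(1 - ρ)). If ρ falls as the interval lengthens, the change becomes noisier. The documents give neither σ nor ρ, so the added noise cannot be sized from them.

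**The case against.** The strongest defence is that the allowance has a purpose. Section 11.4.1.2 states that, once all screening tests and eligibility checks are complete, "Visit 1 can be conducted on the same day to assign participant numbers". An earlier chemistry result lets eligibility be settled at once, so one attendance can replace two. This stands. A reader might infer that the look-back saves nothing and that older results should be barred altogether; the documents do not support that. For eligibility the look-back is a trade-off. There are also other safeguards: the optional retest, the record of history changes between Visits 0 and 1, the exclusion for a history of liver or kidney disease, and the investigator's discretion over laboratory findings.

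A reader might also suppose that the chemistry could be run on the research blood. Section 11.4.2.11 allots all 25 ml (4 × 5 ml EDTA tubes and 1 × 5 ml general tube) to cell isolation and serum, so chemistry needs its own tube. That section describes sampling only at the Kyung Hee centre, and the immunological test schedule gives different sampling times from the Schedule Summary. Those passages need reconciling, but item 9 and the schedule still place a draw at Visit 0.

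A further tempting inference is that stale values bias the comparison of Kyungok-go with placebo. They do not: the rule is the same for both arms and the values precede randomisation.

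Finally, defining the laboratory baseline is commonly left to an analysis plan. That is fair, but an analysis plan can only choose among values that were measured, and under item 9 there may be just one.

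**Conclusion.** The point holds as a minor weakness of the safety baseline. An accepted earlier result can be 35 to 37 days old at first dose on the nominal schedule, or 28 days on the same-day route, against at most 9 days with a panel drawn at Visit 0. The longest before-to-after interval is 28 days longer than it need be. The consequence is noisier change scores, and within-arm paired and McNemar tests that can attribute pre-dose changes to treatment.

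Assumptions:
- The look-back is read as running before screening, which is the natural sense since eligibility must be settled before a participant number is assigned.
- Visit 0 falls on its nominal day -7. No window or maximum screening length is given for it, so 37 days is the scheduled worst case and not a guaranteed ceiling.
- The number of participants who would bring an earlier result is unknown. If none do, nothing changes.

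The protocol does not contradict itself on the chemistry look-back. Its pregnancy-test look-back is anchored to screening in Section 11.4.1.1 and to first administration in Section 11.4.2.12; these two should be reconciled while the item is being edited.

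**What to change.** In Section 11.4.1.1 item 9, require the chemistry panel to be drawn at the Visit 0 venepuncture for every participant, before the first dose. In Section 14.4.2, name that panel as the pre-treatment value. Keep the permission to use earlier results, but limit it to settling eligibility. Same-day enrolment is then unaffected, because a Visit 0 sample is a valid pre-dose baseline even if it is reported later.

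The cost is one extra tube and one chemistry panel for each participant who brings an earlier result, with no extra visit and no extra needle. One consequence needs a sentence in the protocol: a Visit 0 value that meets a laboratory exclusion may come back after randomisation. Section 13 already lists a participant found not to meet the selection criteria among the grounds for discontinuation, and the sponsor should say how that applies here.
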